# Digital home-based physical activity promotion for older adults after total hip arthroplasty: protocol for the randomized controlled iPATH trial

**DOI:** 10.1186/s12877-026-07013-9

**Published:** 2026-01-24

**Keywords:** Hip replacement, Postoperative care, Telerehabilitation, Exercise, Patient education, Sedentary behavior, Ambulatory monitoring, Mobility limitation

## Abstract

**Background:**

Total hip arthroplasty (THA) effectively alleviates pain and improves physical function. However, an increase in patients’ physical activity (PA) is often not observed after surgery. This paradox may result from short rehabilitation periods and persistent sedentary habits and be further influenced by methodological limitations of previous PA monitoring approaches. Digital home-based exercise programs and personal caching (PC) using behavioral change techniques for PA promotion, together with recent advances in PA monitoring, may offer new opportunities to address these challenges. The aim of the iPATH study is to evaluate the efficacy of two novel post-rehabilitation interventions, consisting of a digital home-based physical exercise program with or without PC, compared with usual care, for increasing PA in older adults following THA using advanced PA monitoring approaches.

**Methods:**

In this monocentric, three-arm randomized controlled trial, 213 older THA patients (≥ 65 years) will be assigned in a 1:1:1 ratio post-rehabilitation to a 12-week digital home-based exercise program (“Keep On Keep Up”) with or without additional PC for PA promotion, or usual care. The primary outcome is the mean daily step count at six months post-THA; mean daily walking distance serves as a subordinated primary outcome. Both outcomes will be collected preoperatively, post-rehabilitation, and at six months postoperatively using a body-fixed inertial measurement unit (AX6, Axivity Ltd.) combined with newly validated processing algorithms (Mobilise-D computational pipeline). Secondary outcomes include other digital and self-reported mobility outcomes, physical capacity, hip pain and function, psychological factors, falls, intervention acceptability, and health-related resource use. Primary analyses will follow the intention-to-treat principle.

**Discussion:**

The digital home-based interventions are expected to increase PA compared with usual care. If effective, they have the potential to enhance patient health, reduce morbidity and mortality risk, and be implemented as routine post-rehabilitation care for older adults recovering from THA.

**Trial registration:**

ClinicalTrials.gov (NCT07135843); prospectively registered on August 22, 2025.

**Supplementary Information:**

The online version contains supplementary material available at 10.1186/s12877-026-07013-9.

## Background

Hip osteoarthritis is a leading cause of pain, reduced quality of life and inactivity in older adults. Total hip arthroplasty (THA) is an effective treatment for hip osteoarthritis, alleviating pain and improving physical function [1–3]. Despite these benefits, low levels of preoperative physical activity (PA) often persist after THA. Evidence from systematic reviews and meta-analyses indicates no or only modest increases in PA following THA, with many patients remaining less active than healthy controls during the first postoperative year [4–8]. Low levels of PA are associated with increased morbidity, mortality, and healthcare costs [9–11]. Consequently, the persistence of low PA after THA represents a missed opportunity to improve long-term health outcomes in this patient population.

Postoperative rehabilitation following THA typically consists of inpatient or outpatient programs lasting approximately three weeks [12]. These programs primarily target pain reduction and functional recovery, but may not be specifically designed or primarily intended to promote long-term behavior change or reduce sedentary behavior. This may partly be attributable to the short duration of standard rehabilitation, as habit formation typically requires several months [13]. In addition, compared with healthy individuals, patients undergoing THA and standard rehabilitation continue to exhibit deficits in physical function for up to two years postoperatively [1, 14–16], suggesting that the duration of standard rehabilitation may also be insufficient to fully restore long-term physical function. Evidence from exercise studies in older adults indicates that training durations of several months are typically needed to produce meaningful effects, whereas shorter durations are less effective [17–20]. Extending postoperative rehabilitation to such durations, however, remains largely unfeasible within existing healthcare structures for health-economic and societal reasons.

Self-administered home-based exercise programs may represent a promising approach to support functional recovery after THA, particularly when supported by digital tools [21–23]. In patients undergoing THA, unsupervised home-based exercise programs have been shown to be safe and non-inferior to formal supervised programs delivered in outpatient settings and may therefore constitute a cost-effective strategy for post-rehabilitation care following THA [24, 25]. Digital technologies may facilitate the feasibility, implementation, and effectiveness of such home-based exercise programs by improving accessibility, supporting adherence and motivation through interactive features, and promoting exercise quality through interactive, video-based guidance and training plans [22]. However, evidence-based digital home-based exercise programs alone may be insufficient to sustainably promote habitual PA behavior in daily life among older adults [26].

Personal coaching (PC), a patient-centered process in which a coach supports individuals in changing lifestyle-related behaviors using behavior change techniques (BCTs; e.g., goal setting, self-monitoring, feedback, barrier identification, and problem solving) [27], may offer an opportunity to promote PA among patients following THA. Systematic reviews and meta-analyses have shown that PC incorporating BCTs are effective in increasing PA among older adults [28], persons with physical disabilities [29], and individuals with chronic conditions [30, 31]. However, evidence for the effectiveness of BCTs in promoting PA following rehabilitation for THA is scarce. Previous studies are restricted to case series [32] and a randomized controlled trial (RCT) including mixed lower-limb arthroplasty populations (total hip and knee arthroplasty) and employing only a limited number of BCTs (goal setting, self-monitoring, feedback) [33]. To our knowledge, no methodologically rigorous RCT has yet evaluated the efficacy of PC incorporating multiple BCTs to promote PA in the post-rehabilitation phase among older adults following THA.

Prior research has investigated changes in objective measured PA following THA primarily using basic amount-related PA parameters, such as step count or walking and active duration [4–8]. Recent advancements in sensor technology, combined with newly developed data processing algorithms, now enable valid measurement of a wide range of PA parameters in real-world settings, so-called digital mobility outcomes (DMOs), in both clinical and non-clinical older populations [34, 35]. These DMOs encompass not only the amount of walking (e.g., step count, walking duration), but also walking pattern (e.g., number of walking bouts [WB], WB duration), pace (e.g., walking speed, stride length), rhythm (e.g., cadence, stride duration), and variability (e.g., bout-to-bout variability in walking speed).

The aim of this study is to evaluate the efficacy of two novel post-rehabilitation interventions consisting of a 12-week digital home-based physical exercise program, with or without additional PC, compared with usual care, for increasing PA six months postoperatively among older adults following THA, using advanced PA monitoring approaches. We hypothesize that both interventions will result in greater increases in PA than usual care, with the intervention including PC leading to the greatest improvements.

## Methods

### Study design and setting

The iPATH study (“Digital home-based Physical Activity promotion for older adults after Total Hip arthroplasty”) is a three-arm, assessor-blinded, randomized, parallel-group, monocentric, superiority trial with a 12-week intervention period. Outcomes are assessed 1 week preoperatively (T1), 6 + 2 weeks postoperatively (T2), and 6 months postoperatively (T3; 26 ± 2 weeks). Participant recruitment and on-site outcome assessments will take place at the Department of Orthopaedics, Heidelberg University Hospital, Heidelberg, Germany. Participants will be randomly allocated after T2 to one of two intervention groups (IG) or the control group (CG). The digital interventions will be delivered remotely and implemented at participants’ homes, starting 8 ± 2 weeks after THA following completion of the standard rehabilitation phase. The study flowchart is shown in Fig. 1. The trial was preregistered at ClinicalTrials.gov (NCT07135843) on August 22, 2025. This protocol is reported in accordance with the Standard Protocol Items: Recommendations for Interventional Trials (SPIRIT) guidelines [36].

**Fig. 1 Fig1:**
[figure not shown]
Flowchart of the iPATH study. Abbreviations: *KOKU* Keep On Keep Up, *ITT* Intention-to-treat

### Eligibility criteria and recruitment

Community-dwelling older adults (≥ 65 years) undergoing THA are eligible for inclusion if they are able to walk independently (with or without a walking aid), have internet (WiFi) access at home, and have no visual or hearing impairments, cognitive impairment, pending or incomplete rehabilitation, or severe comorbidities or complications that would preclude participation in an exercise program. An overview of all eligibility criteria is provided in Table 1.

**Table 1 Tab1:** Eligibility criteria for study participation

Preoperative screening		Postoperative screening (4 weeks post-THA)
Inclusion criteria	Exclusion criteria	Exclusion criteria
• Age ≥ 65 years • Coxarthrosis with indication for THA • Residence within a radius of ≤ 50 km from Heidelberg • Ability to walk ≥ 10 m (with/without walking aid) • Access to the internet (WiFi) at home • Written informed consent	• Insufficient German language skills • Insufficient hearing to communicate via (video) telephone • Insufficient vision to recognize study materials • Contralateral coxarthrosis with indication for THA • Severe medical condition that compromises physical fitness (heart failure NYHA ≥ 3, heart valve defects associated with syncope, cardiac arrhythmia with dizziness, COPD with oxygen therapy, cancer with chemotherapy and/or radiation, Parkinson’s disease with rollator use [Hoehn & Yahr stage ≥ 4]) • Living in a nursing home • Planned major medical procedure within the next 6 months with inpatient hospital stay (e.g., further surgery) • Simultaneous participation in another competing study • Cognitive impairment (6CIT ≥ 7 points)	• Ability to walk < 10 m (with/without walking aid) • Post-acute rehabilitation after 6-week postoperative assessment (T2) still pending / not yet completed • Postoperative complications that preclude initiation of the digital exercise program within the next 4 weeks

Abbreviations: *THA* Total hip arthroplasty, *NYHA* New York Heart Association, *COPD* Chronic obstructive pulmonary disease, *6CIT* 6-item Cognitive Impairment Test

Potential participants will be consecutively recruited during routine consultations at the Department of Orthopaedics, Heidelberg University Hospital, Heidelberg, Germany. All patients attending the outpatient clinic will be systematically screened for eligibility using a standardized checklist administered by the secretarial staff. The primary reason for ineligibility will be documented.

Following the initial screening, the study team will verify and complete the eligibility assessment, including cognitive screening using the Six-Item Cognitive Impairment Test [37], and assessment for presence of contralateral coxarthrosis requiring THA. Patients with bilateral coxarthrosis requiring THA on both sides will be placed on a waiting list, and participation may be reconsidered at subsequent surgery if a minimum interval of three months between procedures is met. Patients with coxarthrosis without a current indication for THA will likewise be placed on the waiting list and may be re-screened and enrolled later if a surgical indication arises.

Eligible patients will receive detailed verbal and written information about the study objectives, procedures, potential benefits, and risks. Written informed consent will be obtained preoperatively (T1) by medical staff, following renewed explanation and an adequate reflection period. Formal study inclusion and the T1 assessment will proceed only after informed consent has been obtained.

Approximately four weeks after THA, a postoperative screening will be conducted via telephone to confirm continued study eligibility by verifying ability to walk 10 m with or without walking aid, completion of post-acute rehabilitation, and the absence of postoperative complications that would preclude initiation of the digital exercise program within the following four weeks (Table 1). Only participants who maintain eligibility will proceed to the 6-week postoperative assessment (T2) and randomization.

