### Participant timeline

Eligible participants will complete the preoperative assessment (T1) one week prior to surgery, aligned with their routine preoperative medical consultation. Following THA and standard postoperative rehabilitation (about 3 weeks), participants who remain eligible will undergo the postoperative assessment (T2) at 6 + 2 weeks after THA. After T2, participants will be randomized to the two IGs or the CG. Following randomization, a one-time home visit (approximately 60 min) will be conducted, during which all participants will receive a tablet device with an introduction to its use, and study-arm specific instructions will be provided. During the 12-week intervention period, participants in the IGs will receive their respective intervention components, whereas the CG will receive usual care. Six months (± 2 weeks) after THA, the final assessment (T3) will take place. All assessments will be conducted on site at the Orthopaedic Clinic Heidelberg and will last approximately 1–1.5 h each. A schematic overview of participant flow, enrollment, intervention, and assessment time points is provided in the study flowchart (Fig. 1) and the participant timeline (Supplementary file 1).

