#### Primary outcomes

The first primary outcome is the mean daily step count, and the subordinated primary outcome is the mean daily walking distance. Both DMOs will be recorded with a small (23.0 × 32.5 × 8.9 mm) and lightweight (11 g), water-resistant 6-axis inertial measurement unit (IMU; AX6, Axivity Ltd., Newcastle upon Tyne, United Kingdom), fixed at the participant’s lower back (L5 vertebra) using self-adhesive fixing foil, over a maximum measurement period of 7 consecutive days subsequently to the on-site assessments. After the measurement period, participants will remove the IMU themselves and return it to the study center in a prepaid, pre-addressed envelope. The IMU will be configured with a tri-axial accelerometer (range ± 8 g, accuracy 1 mg) and a tri-axial gyroscope (range ± 2000 dps, resolution 70 mdps), with a sampling frequency of 100 Hz. Raw data from the IMU will be standardized according to a predefined data structure described elsewhere [50]. The Mobilise-D computational pipeline (available at https://github.com/mobilise-d/mobgap), which consists of validated algorithms to derive DMOs [51–53], will then be used to identify WBs [54] and extract number of steps, duration, walking speed, stride length, cadence, and stride duration for each of these WBs. Walking distance per WB will be calculated by multiplying two validated DMOs: average walking speed × WB duration [55]. Steps and walking distances at the WB level will then be aggregated to daily level and averaged across up to 7 valid measurement days to yield mean daily step count and mean daily walking distance. A valid measurement is defined as ≥ 3 valid measurement days; a valid measurement day is defined with ≥ 12 h/day of wear time during waking hours (7 am – 10 pm), without weekday/weekend restriction [56].

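### The exclusion for other planned major procedures can end before the T3 recording does, and neither it nor the contralateral-hip exclusion is among the checks named before randomisation

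*Protocol article*

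**What the plan says.** All references are to the protocol article.

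- **Planned procedures.** Table 1 (Eligibility criteria and recruitment) lists "Planned major medical procedure within the next 6 months with inpatient hospital stay (e.g., further surgery" in the preoperative column only. No start date is given for the six months.
- **Other hip.** The same column lists "Contralateral coxarthrosis with indication for THA", with no time limit. Contralateral disease without an indication is not excluded.
- **When screening happens.** "Potential participants will be consecutively recruited during routine consultations at the Department of Orthopaedics". The study team then verifies and completes the assessment, and formal inclusion takes place at T1. On T1, Participant timeline says: "Eligible participants will complete the preoperative assessment (T1) one week prior to surgery". The interval from consultation to surgery is not stated.
- **Re-screening.** The telephone call about four weeks after THA confirms continued eligibility by "verifying ability to walk 10 m with or without walking aid, completion of post-acute rehabilitation, and the absence of postoperative complications" that would prevent a start of the exercise programme. The postoperative column of Table 1 has the same three items. Only those who stay eligible go on to T2 and randomisation.
- **Endpoint.** T3 is "6 months postoperatively (T3; 26 ± 2 weeks" after THA (Study design and setting). The sensor is worn "over a maximum measurement period of 7 consecutive days subsequently to the on-site assessments" (Primary outcomes).
- **After randomisation.** Statistical analysis applies a treatment-policy strategy to additional interventions, adverse events and new illnesses between T2 and T3. It imputes values missing through dropout or loss to follow-up under missing-at-random.

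**The concern.** The purpose of the planned-procedure exclusion is evidently to keep recovery from a different operation out of the T3 step count and walking distance. Two features stop it from doing so completely. Its clock starts before surgery, while T3 is timed from surgery. And it is asked early, whereas randomisation comes 6 to 8 weeks after surgery, so anything scheduled in between meets no listed check.

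Timing is what makes this worth fixing. A procedure already scheduled before randomisation is a baseline characteristic, and excluding on it costs nothing in validity. Once the patient is randomised, intention-to-treat rightly keeps them. Their T3 value then either reflects recovery from the other operation or is missing and imputed.

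**Working it through.** **1. The plan's own sample size.** Inputs from Sample size: difference 1,500 steps/day, SD 3,000, two-sided 5%, 80% power, independent-samples t-test. The standardised difference is 1,500 / 3,000 = 0.5. The t-test needs 63.8, so 64 per group, and power at 64 is 80.1%. The stated 64 is reproduced. Nothing below changes the planned 64, 71 or 213.

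**2. Where the exclusion window ends.** Six months is 182.6 days / 7 = 26.1 weeks. If the question is asked L weeks before THA, the window ends at post-THA week 26.1 − L. The latest preoperative contact in the article is T1, so L = 1 and the window ends at week 25.1.

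| | T3 at week 24 | T3 at week 26 | T3 at week 28 |
|---|---|---|---|
| End of 7-day recording | week 25 | week 27 | week 29 |
| Gap to T3 visit, weeks | none (−1.1) | 0.9 | 2.9 |
| Gap to end of recording, weeks | none (−0.1) | 1.9 | 3.9 |

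An early T3 is fully covered. A nominal or late one is not.

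**3. If the question is asked before T1.** Each extra week of lead time adds a week to the gap. The article gives no lead time, so these values of L are assumptions. The gap to the nominal T3 visit, L + 26 − 26.1, is 1.9 weeks at L = 2, 3.9 at L = 4, 7.9 at L = 8 and 11.9 at L = 12.

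**4. What is re-asked.** The preoperative items "planned major procedure" and "contralateral indication", set against the three postoperative items (walking 10 m, rehabilitation completed, no precluding complication), have no overlap. From T1 to the call is about 1 + 4 = 5 weeks. From T1 to T2 it is 1 + 6 = 7 to 1 + 8 = 9 weeks. Surgery newly scheduled in that interval triggers none of the listed exclusions.

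**5. Illustrative size.** Suppose a share q of each arm has such surgery and the whole intervention effect is lost in those patients, with the SD unchanged. The mean difference becomes 1,500 × (1 − q). The article gives no value for q.

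| q (assumed) | Difference | Power at 64 per arm |
|---|---|---|
| 0 | 1,500 | 80.1% |
| 2% | 1,470 | 78.5% |
| 5% | 1,425 | 76.0% |

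If half the effect is retained, the difference is 1,500 × (1 − q/2) and power is 79.4% and 78.1%.

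**6. The same under the planned adjusted analysis.** The primary model adjusts for preoperative step count. With an assumed baseline correlation r, the residual SD is 3,000 × √(1 − r²). With the effect fully lost in the share q, power at q = 2% and 5% is 82.2% and 79.8% for r = 0.3, 85.1% and 82.9% for r = 0.4, and 88.8% and 86.8% for r = 0.5.

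**The case against.** **The article already excludes most of these patients.** Anyone with a major inpatient procedure already planned within six months is out, and so is anyone with an indicated contralateral hip, without time limit. Counted from T1, the shortfall against nominal T3 is under a week. This stands, and it is why the point is minor. It does not reach surgery planned for the last weeks before T3 or scheduled after the question was asked.

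**The call is said to confirm continued eligibility, and an article need not print the whole screening form.** This is fair in general. But the sentence says how eligibility is confirmed and names three checks, and Table 1, offered as the overview of all criteria, gives the same three. The form may ask more, but the article does not say so.

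**The planned adjustment for baseline steps offsets the loss.** With a baseline correlation of 0.4 or more, power stays above 80% in both illustrations. This stands as far as it goes, but the correlation is as much an assumption as the rate.

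**A reader might take the three-month rule as evidence that a contralateral operation is expected during follow-up.** It is not. The rule concerns patients with both hips indicated, who go on a waiting list, and says that "participation may be reconsidered at subsequent surgery if a minimum interval of three months between procedures is met". The three months lie before the study operation. The rule governs enrolment at the second hip and lends no support to this point.

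**Conclusion.** The concern holds as a minor mismatch between an exclusion and the endpoint it protects. On the article's own dates, the window ends about 1 week before nominal T3 and up to about 4 weeks before the latest end of the recording. Neither planned procedures nor a new contralateral indication is among the checks named before randomisation. Larger gaps depend on a screening lead time that the article does not state.

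Two stronger readings are not supported. A reader might infer that patients with surgery scheduled before T3 are being randomised. The article shows only that some can be, and says nothing about how many. A reader might also infer that the treatment comparison is biased. Surgery scheduled before allocation is balanced by randomisation in expectation, so the harm is dilution, noise or missing T3 values. The power figures (80.1% to 78.5% or 76.0%) illustrate the scale under an assumed 2% to 5% with complete loss of effect in the unadjusted t-test. They are not estimates.

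**What to change.** Make two changes to the trial's eligibility text:

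1. In the preoperative column of Table 1, replace the six-month window with one that runs to completion of the T3 recording, that is, up to 28 weeks plus 7 days after THA.
2. Add one item to the postoperative screening and confirm it at T2 before allocation: whether any other major inpatient procedure, including contralateral THA, is now planned before the T3 recording is complete.

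The cost is a wording amendment and one question at a call and a visit that already take place. If the amendment counts as substantial, Protocol amendments requires ethics review and a registry update. A few consented patients would be lost before randomisation and need replacing. The 19 participants enrolled by 7 January 2026 were screened under the present wording, but with 213 planned and enrolment running to July 2027, most of the sample would be covered. The sample size and the analysis do not change.
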